### 2.6. Data Collection and Analysis Plan

Patient data, including clinical and demographic information, will be collected and inputted into treatment devices. A unified cloud platform will consolidate information from SH&BA devices and patient clinical data stored across devices. Data from HR sensors will gauge patient therapy adherence.

Descriptive analysis will be initially conducted on the enrolled subjects’ sample. For each demographic and clinical variable, we will consider the mean, standard deviation [23], absolute frequencies (n), and percentages (%). For each mode of clinical treatment delivery (i.e., depending on the physiotherapist/patient ratio), pre-treatment (T0) and post-treatment (T1) motor performance values will be compared using either Student’s t-test for paired data or the Wilcoxon test, depending on the data distribution, which will be assessed with the Kolmogorov–Smirnov test. To assess the presence of a statistically significant difference in motor recovery in relation to the type of treatment model, the motor outcomes of the patients will be compared by means of parametric or non-parametric independent sample comparison tests (i.e., Student’s t-test for independent data or the Mann–Whitney test), depending on the data distribution. To identify the patient profile that best fits each therapy model, regression models will be utilized, with the type of therapy model as the dependent variable, and assessment scales and anamnestic variables as predictor variables. To define the satisfaction, usability and technology acceptance and clinical profile of patients accessing technological therapy, tests for customer satisfaction will be utilized. The statistical significance is set at *p* < 0.05. Data analysis will be conducted using the free statistical software R Studio, version 4.0.3 [24].

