### 2.3. Intervention

Subjects were enrolled among hospitalized patients based on the pre-defined inclusion criteria. The identification of eligible subjects was conducted through notification by the Clinical Research Unit at San Camillo Hospital. Subsequently, researchers from the HosmartAI project will enroll and evaluate (T0) the patients, after which they will commence their experimental treatment in the HR room, in addition to their regular daily conventional rehabilitation session. The experimental treatment will be tailored to the subjects’ therapeutic needs and will run for three weeks, comprising 15 one-hour sessions each, conducted five days a week. The specialized devices targeting balance, manual dexterity, and limb functionality, as described in the study setting section, will be utilized during these sessions. Pre-treatment (T0) and post-treatment (T1) assessments will be conducted using validated clinical scales and tests to determine therapy effects. Additionally, device-specific evaluation systems will be employed to assess treatment outcomes. A qualitative analysis will ascertain technology usability, acceptability, and user satisfaction. All assessments and treatments will be administered by qualified physiotherapists. Figure 1 illustrates the participants’ timeline.

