### 2.4. Outcome and Timelines

The primary aim of the study is to verify the productivity of the rehabilitation service at the IRCCS San Camillo Hospital following the sensorization of the HR with the smart-home system’s devices. Productivity outcomes will be measured through treatment performance, physiotherapists involvement, and adverse events. Assessments will be conducted monthly over a period of one year; the specifics are listed below.

Treatment Performance:Direct measurements of treatments provided in the HR, such as number of treatments provided per month; number of times accessed per month by system users (i.e., patients); number of therapy minutes provided per month and overall therapy duration.

Physiotherapist Involvement:The number of physiotherapists providing treatment relative to the number of patients will be quantified. This ratio (number of physiotherapists/number of patients), will reflect the allocation of staff resources during the study period.

Adverse Events:Measurement and recording of adverse events will involve number of falls occurring during the observation period within the HR.

The following secondary outcomes, changes in clinical parameters following therapies conducted in the HR, as well as satisfaction and user experience associated with the therapy, will also be assessed at baseline (T0) and at the end of the treatment, after 3 weeks (T1).

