### 2.5. Sample Size

The study aims to recruit subjects from IRCCS San Camillo Hospital’s Neurorehabilitation Department. With an average occupancy of 60 beds per week, it is estimated that four eligible subjects are admitted monthly. Given a 20-month trial period, the target sample size was set at 80 subjects. To evaluate the reliability of our study’s results, a retrospective (post-hoc) power analysis was conducted using G*Power 3.1.9.6 software (Heinrich-Heine-University Düsseldorf, Germany). With a two-tailed test, a moderate effect size (Cohen’s d) of 0.5, an alpha level of 0.05, and a total sample size of 80, the analysis yielded a calculated statistical power of 0.99. This suggests a strong probability of detecting the expected effects and highlights the potential dependability of our findings.

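### The between-model comparison needs each patient in exactly one delivery mode, but the physiotherapist/patient ratio that defines the mode is fixed only as a monthly service measure

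*Protocol article*

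**What the plan says.** All references are to the protocol article.

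- **Section 2.6 (Data Collection and Analysis Plan)** makes the delivery mode the grouping variable: "For each mode of clinical treatment delivery (i.e., depending on the physiotherapist/patient ratio), pre-treatment (T0) and post-treatment (T1) motor performance values will be compared". The within-mode comparison is a paired t-test or Wilcoxon test. Motor outcomes are then compared between treatment models with an independent-samples t-test or Mann–Whitney test. A regression with the therapy model as dependent variable follows, to profile which patients suit which model.
- **Section 2.4 (Outcome and Timelines)** holds the only definition of the ratio, as a productivity outcome assessed monthly for one year: "This ratio (number of physiotherapists/number of patients), will reflect the allocation of staff resources during the study period".
- **Section 2.3 (Intervention)** describes a course that "will run for three weeks, comprising 15 one-hour sessions each, conducted five days a week", tailored to the individual patient.
- **Section 2.5 (Sample Size)** gives the enrolment rate: "it is estimated that four eligible subjects are admitted monthly".
- **Section 2.1 (Study Setting and Design)** describes a single-group design. The **Discussion** says that the running of sessions is personalised, and refers to group therapy sessions.

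**The concern.** A physiotherapist/patient ratio belongs to a session, or to the service over a period. A T0–T1 change belongs to a patient over a whole course. The tests in section 2.6 join the two as if each patient carried one ratio throughout. The article gives no allocation to modes, no list of modes, no cut-off, and no statement that a patient's ratio is held constant.

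If a patient is treated alone on some days and in a group on others, the analyst has three choices under the stated tests:

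- Count the patient in both modes, so that the samples are no longer independent.
- Force the patient into one mode, which dilutes the contrast.
- Drop the patient, which costs power.

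Section 2.6 does not choose among these, and a choice made after the data are seen could shape the result. The two-sample test is the only planned test of whether motor recovery differs by treatment model. The therapy-model regression asks a different question, and it too needs one label per patient.

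**Working it through.** **1. The plan's own figures.** Section 2.5 gives 4 patients per month × 20 months = 80, which reproduces. Its power inputs are two-sided alpha 0.05, d = 0.5 and N = 80. For a paired t-test on all 80 (noncentral t, df = 79, noncentrality 0.5 × √80 = 4.47) the power is 0.993, which matches the stated 0.99. That figure therefore describes the T0–T1 test on the whole sample, not the between-model test.

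**2. What each analysis in section 2.6 needs, against what the article supplies.**

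| Analysis | Needs | Supplied |
|---|---|---|
| Paired test within mode | One mode per patient over the course | No patient-level rule |
| Two-sample test between models | Exactly two exclusive groups | Number of modes and cut-off not given |
| Regression on therapy model | One label per patient | Ratio defined only as a monthly service measure |

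**3. Does the enrolment rate show how many patients would be mixed?** Four per month is 4 × 12 / 365.25 × 7 = 0.92 per week. With three-week courses the mean number of concurrent study patients is 3 × 0.92 = 2.76. That mean is all the rate fixes.

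To go further, assume that the ratio follows the number of concurrent study patients, with fixed staff and everyone treated together. Simulating 80 fifteen-weekday courses gives the share of patients whose ratio changes during the course:

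| Start pattern (assumed) | Any change in concurrent number | Change between alone and two or more |
|---|---|---|
| Random, any weekday | about 99% | about 20% |
| Random, weekly start day | about 90% | about 12% |
| Evenly spaced, weekly start day | about 20% | 2.5% |
| Four start together each month | 0% | 0% |
| Mode set per patient and held | 0% | 0% |

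The even-spacing row is itself fragile: starts on any weekday, instead of one fixed day, take it above 90%. The answer depends on scheduling, staffing and cut-offs that the article does not give.

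**4. What is at stake if some courses are mixed.** Between-model power at d = 0.5 (noncentral t, noncentrality 0.5 × √(n1·n2/(n1+n2))):

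- All 80 patients: 0.60 at 40/40, 0.48 at 60/20, 0.31 at 70/10.
- With mixed patients dropped: 0.48 at 30/30, 0.34 at 20/20.

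For forced classification, suppose the effect is linear in the share of sessions, and patients labelled with either mode spend on average a share m of their sessions in the other. The group means then differ in exposure by (1 − m) − m = 1 − 2m. With m = 0.20, d = 0.5 becomes 0.5 × 0.6 = 0.3. The value of m is illustrative; no figure for it is in the article.

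**5. The alternative model.** Regress T1 on T0 and x, where x is the patient's share of attended sessions in one mode. If every patient stays in one mode, x is 0 or 1 and the coefficient of x is the baseline-adjusted difference between the two groups. If not, mixed patients enter at their actual exposure.

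**The case against.** The strongest reply is that the article never says that a patient's ratio changes during the course. Using the therapy model as a regression outcome, to find which patients suit it, fits a mode chosen once per patient and kept. Tailoring to need fits that too. On this reading nobody is mixed and the tests work. A classification rule, such as planned mode at T0 or predominant mode over attended sessions, would also give exclusive groups, and could sit in a full protocol or analysis plan that is not shown. Motor outcomes are secondary in a pilot whose primary aim is productivity.

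Much of this stands. A reader might infer from four admissions a month and three-week courses that many patients must fit no single mode, or that the comparison has no valid groups. The article supports neither. The rate fixes a mean and nothing more, a change in the number of patients enrolled is not a change in anyone's delivery mode, and valid groups can be made by rule.

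What the reply does not remove is the mismatch in the text itself. Section 2.6 commits to tests that presuppose a patient-level mode, while the only definition of the ratio describes the service by month. A cut-off added later would not settle mixed courses unless it came with a rule for them.

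**Conclusion.** The point holds in this form: the grouping variable for the between-model test is not fixed at patient level, and the stated test cannot handle a patient whose ratio varies over the 15 sessions. The number of such patients is unknown. Under the assumptions shown it lies anywhere from 0% to 99%, or from 0% to about 20% if only individual and group treatment are distinguished, and it is zero if the mode is set per patient and held. The consequence is limited to a secondary comparison, but one with little power to spare: at most about 0.60 at d = 0.5 with all 80 patients. The change is worth making because it costs little and does no harm if modes turn out to be constant.

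**What to change.** In section 2.6:

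1. Replace the unadjusted two-sample comparison with a regression of the T1 score on the T0 score and a per-patient exposure. The exposure is either the share of attended sessions at each ratio (one ratio left out as reference) or the mean number of patients per physiotherapist over attended sessions.
2. Build the exposure from the session records and access-badge data that the room is already meant to collect.
3. Report how many patients had mixed courses. Where a single label is still wanted, for the within-mode tests and the therapy-model regression, set the rule in advance (planned mode at T0, or predominant mode).
4. Label the comparison non-randomised and exploratory. Delivery is tailored, so patients treated at different ratios may differ in ways that adjustment for T0 does not remove.

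The cost is a change of wording and one derived variable per patient. The downsides are small: the model assumes that the effect is linear in exposure, and its coefficient is less simple to present than a difference between two groups.

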### 2.2. Participants and Eligibility Criteria

The study will enroll 80 subjects among the patients hospitalized at the IRCCS San Camillo Hospital in Venice. Inclusion criteria for enrolment include an age greater than 18 years and a diagnosis of neurological pathology, such as ischemic and/or hemorrhagic stroke, Parkinson’s disease, multiple sclerosis, head trauma, brain tumor, ataxia, post-COVID syndrome, or peripheral neuropathy. Exclusion criteria include non-stabilized fractures, severe depression, significant visual and/or hearing impairments, dementia, uncontrolled epilepsy, severe neglect, and profound comprehension deficits that would hinder interactions with robotic and virtual reality devices.

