Future implications include profiling patient suitability for this organizational model and its transferability to other rehabilitation settings. However, it is important to acknowledge the limitations of this study, such as the need for expert physiotherapists and potential enrolment complexities, as well as the inherent constraints of pilot studies, including small sample size, a lack of control groups, and limited generalizability. Nevertheless, despite these limitations, the study’s findings are expected to inform and facilitate similar technology implementations in various rehabilitation medical centers. One of the most significant implications is the potential for personalized therapeutic approaches which could concurrently enhance operational efficiency. Specifically, the implementation of SH&BA therapies within technological group treatments for neurological subjects holds promise for augmenting therapy quantity, thereby potentially improving clinical outcomes [28]. This envisaged scenario would unfold alongside resource optimization efforts, aiming to enhance the precision and reliability of collected data and administered therapies, while also striving to mitigate errors. Furthermore, enhancing the patient experience is indeed a significant aspect. The integration of smart-home technologies provides the potential to enhance the overall patient experience during the rehabilitation process. By offering a more comfortable and familiar environment for therapy, it enables greater autonomy and control throughout the healing journey. Moreover, the consideration of patients’ social interaction during group therapy sessions, which also contributes to clinical improvement, further underscores the holistic approach to patient care [29]. Lastly, the remote monitoring capabilities of these systems could expand access to rehabilitation services, particularly for patients in remote or disadvantaged areas.

Disseminating these results nationally and internationally underscores the project’s significance. Efforts to address these limitations and refine the methodology will be crucial in maximizing the impact and applicability of the study’s findings.

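### Motor change from T0 to T1 is analysed within and between delivery modes without using diagnosis, so if change differs by diagnosis the pooled result depends on case mix and the between-mode comparison is confounded

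*Protocol article*

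**What the plan says.** Section 2.2 of the protocol article admits adults with a neurological pathology and names eight examples: "ischemic and/or hemorrhagic stroke, Parkinson’s disease, multiple sclerosis, head trauma, brain tumor, ataxia, post-COVID syndrome, or peripheral neuropathy". It sets no quota, stratum or time since onset.

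Section 2.6 describes three analyses that bear on motor recovery:

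- Within each mode: "For each mode of clinical treatment delivery (i.e., depending on the physiotherapist/patient ratio), pre-treatment (T0) and post-treatment (T1) motor performance values will be compared". The method is a paired t-test or its rank counterpart, whichever suits how the values are distributed.
- Between treatment models: an independent-sample comparison, "Student’s t-test for independent data or the Mann–Whitney test".
- A regression to profile patients, "with the type of therapy model as the dependent variable, and assessment scales and anamnestic variables as predictor variables".

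None of the three uses diagnosis to explain motor change. The first two take no covariate. The third has the therapy model as its outcome, so it describes who received which model and leaves the estimate of motor change as it was.

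Section 2.5 assumes one effect, "a moderate effect size (Cohen’s d) of 0.5", for the whole sample of 80. Section 2.4 makes motor function a secondary outcome; the primary aim is productivity of the service. In the Discussion the authors look ahead: "Future implications include profiling patient suitability for this organizational model and its transferability to other rehabilitation settings".

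**The concern.** Stroke, head trauma, Parkinson's disease, multiple sclerosis and brain tumour need not change by the same amount over three weeks. If they do not, two problems arise.

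First, the mean change within a mode is a weighted average, and the weights are whichever diagnoses happened to be admitted. Another hospital with a different ward population would see a different figure from the same therapy. The result would also say little about who benefits, which is what later profiling and transfer would need.

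Second, the design is single-group and describes no random allocation to delivery mode, while section 2.3 says that treatment is fitted to each patient's needs. Diagnosis may therefore differ between modes. An unadjusted two-sample test would then attribute to the mode what belongs to the diagnosis. This is the more serious of the two problems, because it biases a comparison that the plan itself sets out to make.

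**Working it through.** **Inputs from the article.** N = 80 and alpha 0.05 (section 2.5), "With a two-tailed test", d = 0.5, at least eight diagnoses, grouping by mode only.

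**Assumptions, because the article gives no figures.** Two delivery modes of 40 patients. Two diagnosis classes, with a within-class SD of change of 1. Class A gains g = 0.5 (the article's own d) or 0.8, and the rest are unchanged unless stated. The t-test versions of the planned tests are used.

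**The plan's own figure.** For a paired t-test on all 80, the noncentrality is 0.5·√80 = 4.47 with 79 df, giving power 0.993. The stated 0.99 is reproduced. It belongs to one paired test on all 80 with one common effect. Section 2.6 tests within mode, so 40 per mode is used below.

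**Step 1: pooled test within a mode.** With share s in class A, gain g there and g0 in the rest:

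- mean change m = s·g + (1 − s)·g0
- SD of change = √(1 + s(1 − s)(g − g0)²)
- pooled d = m/SD, noncentrality d·√40, 39 df

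| g | g0 | Share of class A | Mean change | Pooled d | Pooled power, n = 40 | Class A alone (n), power |
|---|---|---|---|---|---|---|
| 0.5 | 0 | 30% | 0.15 | 0.146 | 0.15 | (12) 0.35 |
| 0.5 | 0 | 50% | 0.25 | 0.243 | 0.32 | (20) 0.56 |
| 0.5 | 0 | 70% | 0.35 | 0.341 | 0.56 | (28) 0.72 |
| 0.8 | 0 | 30% | 0.24 | 0.225 | 0.28 | (12) 0.71 |
| 0.8 | 0 | 50% | 0.40 | 0.371 | 0.63 | (20) 0.92 |
| 0.8 | 0 | 70% | 0.56 | 0.526 | 0.90 | (28) 0.98 |
| 0.8 | −0.2 | 50% | 0.30 | 0.268 | 0.38 | (20) 0.92 |

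With the effect in class A held fixed at 0.8, the pooled mean runs from 0.24 to 0.56 SD on case mix alone. At a low share the gain is likely to be missed. At a high share a significant result would be read as applying to everyone.

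**Step 2: the same sum when the classes behave alike.** With a common d = 0.5, the pooled test at n = 40 has power 0.87 and each class of 20 has 0.56. With gains of 0.6 and 0.4 in equal halves, the pooled test has 0.87, against 0.72 and 0.40 for the classes. Separate tests by diagnosis would be worse still: 80/8 = 10 each gives power 0.29 at d = 0.5.

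**Step 3: between-mode test with no true mode effect.** Class A makes up 70% of one mode and 30% of the other.

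- Expected difference: (0.7 − 0.3)·g = 0.20 (g = 0.5) or 0.32 (g = 0.8).
- SD within a mode: √(1 + 0.21·g²) = 1.026 or 1.065.
- Standardized difference: 0.195 or 0.300.
- Noncentrality: multiplied by √(40/2), 0.87 or 1.34 with 78 df.
- Rejection rate: 0.14 or 0.26.

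Simulation of 20,000 trials agrees when each patient's class is drawn at random (0.14 and 0.26). It gives 0.13 and 0.25 when the shares are exactly 28:12 and 12:28. Adding class to the model brings the rate back to 0.05 in every case. With shares of 60% against 40% the unadjusted rate is 0.07 or 0.10; with equal shares it is 0.05.

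**The case against.** The strongest reply has four parts.

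- **This is detail for the analysis plan.** Covariates and subgroup reporting are often left there. That does not dispose of the point: the article names tests that take no covariate, so bringing in diagnosis means changing a stated method.
- **The premise lies outside the article.** It states no expected course, time since onset or case mix. This stands. If diagnoses change alike, pooling does no harm and is more powerful (Step 2). Setting the pooled test against the improving class alone also presumes that one knows beforehand which class improves.
- **The average over a mixed ward is a legitimate target.** For a study of a service this is fair, and the paired test estimates that average validly. It supports keeping the overall mean, but does not rescue the between-mode comparison, where a difference in mix is bias.
- **The stakes are limited.** Motor change is secondary, the study is a pilot, and the Discussion concedes small size, no controls and limited generalizability. This lowers the weight of the point. Conceding generalizability does not, however, address confounding between modes.

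A reader might infer that the planned tests will hide a real gain in one class and also credit it to all. The article does not support that. For a given test, hiding goes with a non-significant result and over-crediting with a significant one. Which occurs depends on the mix, and neither occurs if the classes change alike. Nor does the article say that a pooled change will be claimed for every diagnosis; its remark on profiling and transfer concerns future work.

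**Conclusion.** The point holds in conditional form. As written, no analysis of motor change uses diagnosis, although at least eight diagnoses are admitted and no random allocation to mode is described.

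If change differs by diagnosis, the within-mode result depends on case mix: pooled power runs from 0.28 to 0.90 as the share of a class gaining 0.8 SD goes from 30% to 70%. The between-mode test has a false-positive rate of about 13% to 25% at class shares of 70% against 30%, 40 per mode and a class gain of 0.5 to 0.8 SD. These sizes illustrate the problem and do not predict it: the class shares, class gains and mode sizes are all assumed. The error falls to 7% to 10% at shares of 60% against 40%, and disappears if either the mix or the changes are equal.

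The change is worth making because it is cheap and protects a planned comparison. It does not touch the primary outcome.

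**What to change.** In section 2.6, analyse the T0–T1 change in each motor scale in one model with two factors: delivery mode and a diagnosis class fixed in advance. Assign every admitted diagnosis to a class beforehand, including those that fit no obvious group, such as ataxia, post-COVID syndrome and peripheral neuropathy.

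Report:

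- the overall mean change, as now;
- the between-mode difference adjusted for class;
- the mean change in each class with its 95% confidence interval, as description;
- the difference in change between classes (the class-by-time interaction) with its interval.

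Do not claim improvement according to which class reaches significance; with classes of this size that would mostly reflect their numbers. State that, without a control group, change within a class cannot be separated from natural course. Adjustment for diagnosis does not cure that.

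**Cost.** Wording only: diagnosis is needed for eligibility, and section 2.6 already collects clinical data. Intervals are wider per class than for the pooled mean, and the class definition must be settled before the data are seen. The adjusted mode contrast is slightly less precise when mode and class are related. At 70% against 30% their correlation is 0.4, so its standard error grows by a factor of about 1/√(1 − 0.16) = 1.09, before any gain from the smaller residual variance.

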## 2. Materials and Methods

### 2.1. Study Setting and Design

To ensure the completeness and quality of reporting, we referred to the SPIRIT (Standard Protocol Items: Recommendations for Interventional Trials) [9] guidelines as well as Thabane and Lancaster’s [10] guidance on how to report protocols of pilot and feasibility trials. The protocol was registered in the ClinicalTrials.gov PRS database (Registration number: NCT06270420, https://clinicaltrials.gov/study/NCT06270420, accessed on 22 February 2024). This single group, pre-post longitudinal pilot study will be conducted within the HosmartAI research project (EU Horizon 2020, research and innovation program—grant agreement No 101016834). The trial will last twenty months and will be carried out at the San Camillo IRCCS Hospital (Venice, Italy), within which a smart rehabilitative room (HR) will be created. This room will feature rehabilitation devices complemented by smart-home sensors and actuators developed by VIMAR SpA (Marostica, Italy), all of which send data to a cloud system (Kloud) created by Khymeia Group (Padua, Italy). The purpose of this setup is to develop an innovative solution to monitor various activities that patients can perform autonomously or under therapists’ supervision. This solution aims to assist clinicians in monitoring patients within the hospital, identifying potential risks, and ensuring adherence to therapy protocols. Throughout the pilot phase, stakeholders involved will be closely observed using a persona-based approach, providing valuable insights into the behaviors of therapists and patients, thus enabling the analysis and exploration of the extension of active patient monitoring to the home environment.

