## 3. Discussion

This pilot study protocol outlines a structured approach to investigate the integration of SH&BA systems in neurorehabilitation, aiming to provide insights into the potential benefits and challenges of this innovative approach. Findings from this pilot study may inform the design of larger-scale trials and guide the implementation of smart-home technology in clinical practice, ultimately enhancing rehabilitation outcomes for individuals with neurological impairments.

With the ongoing advancements in digital healthcare, integrating into rehabilitation processes is crucial for enhancing patient care outcomes and management efficiency [6,7,8]. This study aims to combine technology with clinical requirements by sensorizing the environment. This enables the tracking of the number of eligible patients treated, the actual physiotherapy hours, and the ratio of physiotherapists to patients, all within existing financial constraints. By comparing pre-project data with the acquired results, potential savings of around 20–30% for the facility can be estimated. However, realizing the full potential of smart-home technologies in healthcare requires robust research methodologies and ethical considerations regarding data privacy. Continued research and development in these areas are essential to further optimize these technologies and maximize their benefits for patients and healthcare systems alike [25,26,27]. The study’s novelty lies in achieving cost savings while increasing productivity without compromising clinical outcomes. Personalized treatment remains paramount, ensuring patient-centric care through tailored device selection, exercise settings, and session management. Thus, even in the worst-case scenario, clinical outcomes are expected to be maintained, if not improved. Additionally, assessing device usability and patient satisfaction will validate the model’s viability. This project addresses the pressing need for increased therapy hours without escalating healthcare costs. Recruiting staff can be challenging, particularly in hard-to-reach areas, yet high-intensity rehabilitation centers, like San Camillo Hospital, must prioritize therapy hours. Balancing these needs requires economically feasible and qualitatively robust solutions, which this trial aims to provide.

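### Motor recovery is compared between non-randomised treatment models with unadjusted two-sample tests, so a baseline or diagnosis difference between models can bias the comparison

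*Protocol article*

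**What the plan says.** Section 2.1 gives the design: "This single group, pre-post longitudinal pilot study will be conducted within the HosmartAI research project". No section describes randomisation, or any rule, that puts a patient into one delivery model rather than another.

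Section 2.6 defines the models when it introduces the paired T0-T1 tests: "For each mode of clinical treatment delivery (i.e., depending on the physiotherapist/patient ratio". It then states the aim of the between-model analysis, "To assess the presence of a statistically significant difference in motor recovery in relation to the type of treatment model", and the method: "the motor outcomes of the patients will be compared by means of parametric or non-parametric independent sample comparison tests", namely Student's t-test or the Mann-Whitney test according to the distribution. No covariate is named. The only regression in the section has therapy model as the dependent variable and assessment scales and history as predictors; its purpose is to find which patient profile suits which model.

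Three other statements bear on whether the models hold comparable patients:
- Section 2.3: "The experimental treatment will be tailored to the subjects’ therapeutic needs", and it is given "in addition to their regular daily conventional rehabilitation session".
- Section 3 speaks of "ensuring patient-centric care through tailored device selection, exercise settings, and session management".
- Section 2.2 admits a wide case mix, including "ischemic and/or hemorrhagic stroke, Parkinson’s disease, multiple sclerosis, head trauma, brain tumor, ataxia", as well as post-COVID syndrome and peripheral neuropathy.

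**The concern.** An unadjusted two-sample test reads any difference between groups as going with the group label. That is safe when allocation is random. Here it is not random, and the profiling regression shows that the authors consider it worth asking whether patient characteristics differ between models. That regression cannot help the motor comparison, because the model is its outcome and not one of its predictors.

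This is the only planned contrast of motor outcomes between patients. It bears on the claim in section 3 that productivity can rise without loss of clinical outcome. A T0 imbalance could produce a spurious difference between staffing models or hide a real one. The method is stated, not left open, so an analysis plan that added covariates would contradict the article.

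**Working it through.** **The plan's own figure.** Section 2.5 gives power 0.99 for n = 80, d = 0.5, two-sided alpha 0.05. For a paired test the noncentrality is 0.5 × √80 = 4.47 on 79 df, and power is 0.993, so the figure reproduces. It belongs to the paired T0-T1 test on all 80 patients. For the between-model test the noncentrality is d × √(n1·n2/(n1+n2)). At 40/40 this is 0.5 × √20 = 2.24 and power is 0.60; at 20/60 power is 0.48.

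**Assumed inputs, none given in the article.** Two models; 40 patients in each; T0 gap D between models; T0-T1 correlation r; no true model effect; T0 the only confounder. With within-group SD 1 at both times, T1 = r·T0 + √(1 − r²)·noise.

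**Bias.**
- T1 compared: the expected difference is r·D, in favour of the group that starts better.
- Change compared: the expected difference is (r − 1)·D, against that group. The SD of change is √(2(1 − r)).
- The rejection rate follows from the noncentral t on 78 df with noncentrality (standardised bias) × √20.

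**Results for D = 0.5.**

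| r | Comparison | Bias (SD of score) | Standardised bias | Noncentrality | Rejection rate |
|---|---|---|---|---|---|
| 0.7 | T1 | +0.35 | 0.350 | 1.57 | 34% |
| 0.7 | Change | −0.15 | −0.194 | −0.87 | 14% |
| 0.8 | T1 | +0.40 | 0.400 | 1.79 | 42% |
| 0.8 | Change | −0.10 | −0.158 | −0.71 | 11% |

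Simulation agrees: up to 44% on T1, 10-14% on change, and about 5% for ANCOVA on T0.

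**Sensitivity to the assumed values.** At r = 0.7, a gap of 0.2 SD gives about 10% (T1) and 6% (change); a gap of 0.8 SD gives about 69% and 27%. At D = 0.5, moving r from 0.5 to 0.9 takes the T1 rate from 20% to 51% and the change rate from 20% down to 8%.

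**Masking.** If the lower-staff group started 0.5 SD better and r = 0.8, a model truly 0.4 SD worse would show no difference on T1, since 0.8 × 0.5 = 0.40. On change the same case would show −0.40 − 0.10 = −0.50, an overstatement of the harm.

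**A different form of selection.** Suppose instead that the groups differ stably by 0.5 SD and T0 is measured with error (reliability 0.7-0.8). With no model effect, change scores then hold about 5%, and ANCOVA rejects 11-16%.

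**Precision.** With no imbalance and a true 0.5 SD difference, power at r = 0.7 to 0.8 is 0.60 on T1, 0.81-0.94 on change and 0.87-0.96 with ANCOVA.

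**The case against.** The strongest reply is that selection by severity is an inference. No section says how a patient comes to a given ratio. The tailoring in section 2.3 is described next to the choice of devices, and section 2.4 treats the ratio as a reflection of staff resources, so scheduling could drive it. The profiling regression asks whether profiles differ; it does not assert that they do. This stands, and it makes the bias conditional. It does not make an unadjusted test a sound choice, because the article gives no ground for assuming that the groups are comparable.

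A reader might infer that the less impaired go to the lower-staff model and that this model will therefore be flattered. The documents do not support that. The direction holds only if T1 scores are compared. Section 2.4 lists the clinical outcomes as changes and section 2.6 speaks of recovery, so change is the better-supported reading, and under the same assumptions the bias then runs the other way and is smaller. A reader might also infer that differences will be reported as effects of the model. Section 2.6 uses wording of association, so the most one can say is that they could be read so.

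Nor is ANCOVA a guaranteed cure. Its 5% comes from making T0 the only confounder; under stable group differences with measurement error it does worse than change scores.

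That paired tests cannot separate the smart room from conventional therapy or natural recovery is inherent in a single-group design. It is largely disclosed: section 2.3 states the concurrent sessions and section 3 lists the lack of a control group. Only the description of those results needs care.

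**Conclusion.** The point holds in conditional form. The article fixes an unadjusted test for a non-randomised comparison, and its one regression does not adjust that comparison. Whether bias occurs, how large it is and which way it runs depend on three things that the article does not give: the imbalance between models, the T0-T1 correlation, and whether T1 or change is compared. For a moderate assumed gap of 0.5 SD, with r of 0.7 to 0.8 and a 40/40 split, the false-positive rate is about 34-44% on T1 or about 10-14% on change, against a nominal 5%.

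The primary aim is productivity, and this is a secondary comparison in a pilot. It should be fixed before the analysis, but it does not undermine the study as a whole. The stated power of 0.99 should not be read as applying to this comparison.

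**What to change.** In section 2.6, replace the independent-samples tests with a regression, for each motor scale, of T1 on treatment model, T0 score, age and a few pre-specified broad diagnosis groups. Use ordinal regression for Functional Ambulation Categories, and an ordinal or rank-based regression wherever else the scale or distribution calls for it. The diagnosis groups must be broad: eight conditions are listed, which among 80 patients is an average of 10 each.

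Report the adjusted difference with its 95% CI and call it an observational association. Give the change-score comparison as a sensitivity analysis, because neither method is unbiased under every form of selection; if the two disagree, say so. Describe the paired T0-T1 results as change during combined conventional and smart-room care, not as effects of the smart room.

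The cost is revised wording and slightly more analysis. T0 scores and clinical and demographic data are already to be collected. Confounding by unmeasured factors remains and should be stated.
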